**Methods:**

48 CR participants with cervicobrachial pain (numeric rating scale ≥ 4) will be enrolled in a five-period pilot RCT and randomly assigned to receive either usual care alone or AMT plus usual care for 4 consecutive periods (each period defined as 7 days). The primary outcome will be feasibility, focusing on enrolment rate, retention rate, and protocol adherence. The secondary outcomes include pain in the cervicobrachial region, upper extremity numbness, muscle weakness, upper extremity and neck function, analgesic consumption (non-steroidal anti-inflammatory drugs and opiates), work ability, quality of life, emotional well-being prior to administering treatment at each period’s initial visit, as well as safety and intervention costs during the trial. We employ linear mixed-effect models on the efficacy-related outcome measures to assess the changes within and between groups over time, and determine the statistical trends of effectiveness.

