## Objectives

2

The aim of this external pilot study is to ascertain the feasibility of a definitive full-scale RCT that determines whether AMT plus usual care is superior to usual care alone in clinical efficacy and cost-effectiveness regarding cervicobrachialgia reduction. In this study, we will (1) evaluate the recruitment and retention of participants, treatment adherence, and completion of proposed outcome measures to inform the feasibility and acceptability of study design; (2) and estimate the variability of efficacy-related outcomes to preliminarily inform sample size calculation for a future fully powered RCT.

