### Study design

3.1

The **p**ilot study on **A**ngled **M**anual **T**raction and usua**L** car**E** for cervical **R**adiculopathy (pAMTLER) will be an open-label RCT with two parallel groups and blind evaluation. In this five-period (7 days per period) trial with a total of 15 visits, 48 eligible participants with CR will be enrolled. All enrolled participants will receive usual care for four periods. The 24 participants randomly assigned to the experimental group will also receive 14 sessions of AMT. The baseline will be defined as the pre-treatment assessment during the initial visit in the first period after randomization. Participants will be scheduled to complete the outcome assessments prior to treatment during the initial visit in each period. Figure 1 illustrates the study design. The pAMTLER will be conducted at the Guangdong Provincial Hospital of Chinese Medicine (GPHCM), Guangzhou, China, with approval from the Ethics Committee at GPHCM (approval number: BF2024-156-01). The study protocol was registered with ChiCTR2400087289, and is reported according to the Standard Protocol Items: Recommendations for Interventional Trials (SPIRIT) (31) (Appendix S2). Figure 2 overviews the participant flow and details the assessed content at each scheduled visit (Appendix S3).

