#### Secondary outcome measurements

3.6.2

Measurements intended for efficacy assessment in the future definitive trial will be designated as the secondary outcomes. These secondary outcome measures are scheduled to be assessed prior to treatment administration during each period’s initial visit (as shown in Figure 2), and outlined below:

pain rating with the NRS, including cervicobrachial pain, upper extremity pain, neck pain, and shoulder pain.numbness in the upper extremities graded by the NRS.muscle weakness recorded by grip strength using a hand dynamometer (CAMRY EH101) in kilograms.upper extremity disability assessed by the quick disabilities of the arm, shoulder, and hand questionnaire (QuickDASH)neck disability scoring with the neck disability index (NDI)NSAID and opiate consumption per period documented in patient diaries.work-productivity impairment evaluated with the work productivity and activity impairment questionnaire: cervical radiculopathy (WPAI: CR)quality of life quantified with the 5-level version of the euroqol 5-dimensional descriptive system (EQ-5D-5L)emotional well-being measured by Zung’s self-rating depression scale (SDS) and Zung’s self-rating anxiety scale (SAS)

The NRS is a horizontal bar or line evenly segmented by 11 integers, in which “0” on the far left represents “no pain” while “10” on the far right indicates “the worst pain imaginable” (34). It is a popular scale for quantifying pain intensity without usage barriers across cultures and languages (35), and has also been well-validated among patient populations with musculoskeletal pain (36–40). Participants will be instructed to circle one number on the NRS to represent the amount of pain that they are experiencing at the time of evaluation (40). Clinically meaningful pain relief can be concluded when a reduction of at least 30% or 2 points is observed on the NRS (41). Given its recommendation for assessing non-pain subjective experiences, we employed NRS in our study to quantify numbness in the upper extremities (42).

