The WPAI: CR is a revised questionnaire constructed by specifying “cervical radiculopathy (CR)” in the Work Productivity and Activity Impairment Questionnaire: Specific Health Problem V2.0 (WPAI: SHP). The WPAI: SHP is a six-item patient-reported instrument created for capturing the amount of work time missed, on-the-job effectiveness reduced, and daily activity impairment during the previous 7 days due to a specific health problem (68, 69). The official user guide encourages adapting the WPAI: SHP to any specific health problem by inserting the name of the disease or condition of interest wherever the word ‘PROBLEM’ appears in the WPAI: SHP template (70). In our trial, CR-related work productivity loss will be quantified based on the revised WPAI: CR through per cent work time missed, impairment while working, overall work impairment and activity impairment (71). Greater values indicate less productivity.

Additional secondary outcome measures will include adverse event rate (AER), adverse reaction rate (ARR) and intervention cost. Any undesirable experiences from which participants suffer post-enrolment will be identified as adverse events (AE), and those associated with the intervention will be defined as adverse reactions, while those that result in hospitalization, loss of ability to work, disability, congenital deformity, or death will be listed as serious adverse events (SAE). Any AE during the study will be recorded. The cost of intervention will be based on a societal perspective, and composed of direct medical costs (DMC), direct non-medical costs (DnMC) and indirect costs (IDC) (72). The composition of direct costs are detailed in Table 2, and the composed item cost will be obtained by resource volumes multiplied by their respective unit costs (73). The IDC will be estimated using the human capital approach, which is the product of labor loss time and the unit labor value (72–74). In this trial, labor loss time will encompass the work time missed by both participants and their accompanying family members. The unit labor value will be based on the per capita GDP of Guangzhou in 2024 (73). DMC, DnMC, and the accompanying family’s missed work time will be collected at every visit. The participants’ missed work time will be collected via the WPAI: CR.

**Table 2 tab2:** Composition and determination of direct costs.

Cost composition	Basis for unit cost calculation

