#### Data analysis

3.7.2

Data will be statistically analyzed using PASW Statistics 18.0, STATA 14.0 and R 4.3.0. Continuous variables will be summarized as means with standard deviations or medians with interquartile ranges, whereas categorical variables will be presented as counts and percentages. The primary outcome will be outlined using descriptive statistics. Building on reported positive associations between colder temperatures, male sex, and more consultations for musculoskeletal pain (76), we will conduct subgroup analyses to explore how season and sex influence enrolment, retention, and adherence, thereby informing weather-adaptive management strategies for the future full RCT. Secondary outcome measures will be analyzed based on the intention-to-treat population approach. Any post-randomization participants who received at least one intervention session will be included in the full analysis set. Among these, those who completed at least 80% of the planned treatments without any significant protocol violations will be categorized into the per-protocol analysis set. Any post-randomization participants receiving at least one intervention session will be classified into the safety analysis set. Any missing data will primarily be handled using multiple imputation, with last observation carried forward applied for sensitivity analysis.

We will analyze both within- and between-group changes for each efficacy-related secondary outcome variable using a linear mixed-effects model to derive estimates of intervention effects.

Group allocation, time-point and the interaction between group allocation and time-point will act as fixed-effects, individuals as random effects, and baseline measurements as covariates. Given that this exploratory trial is not formally powered to assess effects, a recommended confidence interval of 75% will be employed to infer the size and direction of the calculated effect estimates (77). The 75% confidence interval will be compared with the MCIDs to preliminarily assess whether the difference between treatment groups holds potential for clinical significance (77). The remaining secondary outcome measures involving AER, ARR, and intervention costs, as well as baseline variables, will be presented descriptively by the groups.

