## Discussion

5

A full RCT with appropriate power is necessary to establish the clear effects of AMT on pain relief and functional improvement in patients with CR. However, such studies conducted over the past decade have been insufficient. Therefore, establishing whether a more extensive future RCT would be viable is of paramount importance (78). The pAMTLER study is a randomized pilot developed to address this issue. It will focus on assessing the ability to enroll CR individuals with moderate-to-severe cervicobrachialgia, to retain participants for the intervention duration, and to encourage participants to adhere to the protocol during the trial, thereby establishing the feasibility of a proposed full-scale RCT. Meanwhile, the pAMTLER study can provide preliminary data on the efficacy and safety of AMT for CR, thereby complementing the key estimates regarding outcome variability necessary for sample size calculations in the confirmatory trial.

Several advantages make the pAMTLER study instructive for a future definitive RCT on AMT for CR. To begin, the pAMTLER study meets the methodological requirements for feasibility and pilot projects. It was carefully designed, not only with adequate randomization, allocation concealment, and blinding of outcome assessors and statisticians, but also specifying clear feasibility objectives, analytic plans, and criteria for the success of feasibility (80). Additionally, with small feasibility study samples, confidence intervals for clinically important differences in outcomes of interest are narrowed to a 75% confidence level. Such analytical strategies are justified, contributing to realistic and unbiased effect estimates to inform subsequent power calculation for the future full definitive RCT (77, 79). Third, unlike most previous RCTs which directly compare different multimodal conservative strategies for CR patients (20, 81), the pAMTLER study is characterized by a randomized add-on trial. An add-on study design could be more rational in circumstances where analgesics are commonly preferred as the first-line therapy (82), while also allowing for further understanding of AMT’s superiority in real-world clinical practice of CR.

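### The 75% interval is read for size and direction on every efficacy outcome with no key outcome or time named, so an isolated favourable interval is weak evidence for AMT

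*Protocol article*

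**What the plan says.** Section 3.7.2 sets the scope of the efficacy analysis: "We will analyze both within- and between-group changes for each efficacy-related secondary outcome variable using a linear mixed-effects model". The fixed effects are group, time-point and their interaction, with baseline as covariate. The same section calls the trial exploratory and not powered for effects, and then gives the reading rule: "a recommended confidence interval of 75% will be employed to infer the size and direction of the calculated effect estimates". The next sentence adds that this interval will be compared with the MCIDs to judge potential clinical significance. No outcome or time-point is singled out for either reading.

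The number of contrasts follows from sections 3.1 and 3.6.2. Several listed outcomes carry more than one score, for example "pain rating with the NRS, including cervicobrachial pain, upper extremity pain, neck pain, and shoulder pain" and, for the work-productivity questionnaire, "per cent work time missed, impairment while working, overall work impairment and activity impairment". On timing, section 3.1 says: "Participants will be scheduled to complete the outcome assessments prior to treatment during the initial visit in each period". With five periods, and baseline taken at the start of the first, there are four post-baseline assessments.

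The use to be made of the results is described unevenly. The abstract's Methods say the models will "determine the statistical trends of effectiveness", and its Results place better health outcomes under AMT among the successful pilot targets, beside enrolment, adherence and retention. Section 4 gives only the three feasibility targets and presents better outcomes as a hypothesis. Section 5 says of the 75% level: "Such analytical strategies are justified, contributing to realistic and unbiased effect estimates to inform subsequent power calculation". Section 2 already points to one efficacy question for the future trial, whether AMT plus usual care is "superior to usual care alone in clinical efficacy and cost-effectiveness regarding cervicobrachialgia reduction".

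**The concern.** A 75% interval excludes zero in AMT's favour far more often by chance than a 95% interval does: 12.5% against 2.5% per contrast. That is defensible for one pre-named contrast in a pilot. Here the reading covers every efficacy score, and the group-by-time term gives up to four between-group contrasts for each. The text leaves open which of them supports a trend, or the abstract's efficacy target. A report could therefore point to whichever interval looks favourable, and a reader could not tell how surprising it is.

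The section 5 statement is a separate matter of fact. The confidence level does not enter the point estimate. If effects were carried into the next trial's power calculation because their intervals looked favourable, they would be biased upward, whatever the level.

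**Working it through.** The plan states no false-positive rate for the 75% reading, so there is no figure of its own to reproduce.

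**Inputs from the protocol article**
- Level 75%, so z = 1.150 and the favourable tail is 0.25 / 2 = 0.125 (section 3.7.2).
- Scores (section 3.6.2): 4 pain NRS + numbness + grip strength + QuickDASH + NDI + NSAID use + opiate use + 4 work-productivity scores + EQ-5D-5L index + EQ-VAS + SDS + SAS = 18.
- Post-baseline assessments: 5 − 1 = 4. Contrasts: 18 × 4 = 72. Reading each time separately is inferred from the interaction term; the article does not say so.
- 24 participants per arm (section 3.1).

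**Assumed, because the article gives no figure:** correlations of the estimates between outcomes and between times, and outcome SDs.

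**Step 1. Expected number under no effect.** 72 × 0.125 = 9 favourable intervals on average, whatever the correlation.

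**Step 2. At least one favourable interval under no effect.** If independent, the probability is 1 − 0.875^k: 0.910 for k = 18 and above 0.999 for k = 72. Correlation lowers it. Simulated normal test statistics, counting z > 1.150, gave:

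| Correlation between outcomes | One assessment, 18 contrasts | Four assessments, 72 contrasts (equal correlation between times of 0.5 / 0.7 / 0.8) |
|---|---|---|
| 0.3 | 0.70 | 0.95 / 0.91 / 0.88 |
| 0.5 | 0.57 | 0.87 / 0.80 / 0.77 |
| 0.7 | 0.43 | 0.75 / 0.68 / 0.63 |
| 0.8 | 0.35 | 0.66 / 0.59 / 0.55 |

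With correlation decaying between successive assessments instead, the 72-contrast figure is 0.96 (outcomes 0.3, adjacent times 0.5), 0.84 (0.5, 0.7) and 0.64 (0.7, 0.85). Counting only the nine listed outcome entries at four times gives 0.48–0.86.

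**Step 3. One pre-named contrast.** With 24 per arm and standardised effect d, the favourable probability is about Φ(d√12 − 1.150). For d = 0 it is 0.125. For d = 0.5 it is Φ(1.732 − 1.150) = 0.72. For d = 0.8 it is Φ(2.771 − 1.150) = 0.95. A single named contrast does separate a null from a moderate effect.

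**Step 4. The MCID comparison under no effect.** SE = SD × √(2/24) and half-width h = 1.150 × SE. The chance that the interval both excludes zero and reaches the MCID is 1 − Φ(max(h, MCID − h)/SE). For NRS with MCID 2 and SD 2.5: SE = 0.722, h = 0.830, (2 − 0.830)/0.722 = 1.62, giving 5.3%.

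| Outcome (stated MCID) | Assumed SDs | Chance per contrast |
|---|---|---|
| Pain NRS (2) | 2 / 2.5 / 3 | 1.0% / 5.3% / 12.3% |
| NDI (7) | 6 / 8 / 10 | 0.2% / 3.0% / 10.1% |
| QuickDASH (14) | 12 / 16 / 20 | 0.2% / 3.0% / 10.1% |

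The whole interval lies beyond the MCID in under 0.1% of null cases at these SDs. Grip strength, analgesic use, work productivity, EQ-5D-5L, SDS and SAS have no stated MCID, so for them only the direction reading remains. The NRS figure is worded as a reduction in pain, not as a difference between groups.

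**Step 5. Would 95% intervals alone be enough?** Over all 72 contrasts, at least one would still favour AMT in about 21–58% of null trials under the equal-correlation grid. The protection comes from naming one contrast and labelling the rest descriptive, not from the level.

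**The case against.** The strongest reply is that the article contains no rule under which any one favourable interval counts as success. It calls the analysis exploratory, makes feasibility primary, and promises no error control. That stands: the 55–96% range describes a reading the text permits, not one it prescribes. A reader might infer that the 75% interval cannot distinguish a useful AMT from a useless one. The documents do not support that, since a single contrast is favourable in 12.5% of null trials against 72% at d = 0.5, and the mean number of favourable contrasts is 9 against about 52 of 72.

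The MCID comparison is a real filter and must be credited, though it covers only three instruments. A reader might also take the 75% reading as the only route to a definitive trial; section 4 sets go and stop thresholds on feasibility alone. Nor is efficacy read at all 15 visits: there are four post-baseline assessments. Selecting outcomes by their intervals is a risk the wording leaves open, not a stated intention.

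Emphasis among outcomes is often left to an analysis plan. Here, however, the article itself fixes the level, the scope and the purpose, and its abstract attaches an efficacy target.

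**Conclusion.** The point holds in limited form and should be corrected. The 12.5% null rate per contrast follows from the level itself. The 55–96% range (all 72 contrasts) and the 43–70% range (last assessment only, outcome correlations 0.3–0.7) rest on assumed correlations and on my count of 18 scores; at an outcome correlation of 0.8 a single assessment gives 35%. An isolated favourable 75% interval is therefore weak evidence, particularly where no MCID is stated.

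Two parts need no assumptions. The abstract and section 4 disagree on whether better outcomes are a success target or a hypothesis. Section 5 credits the 75% level with contributing to unbiased estimates, which no confidence level can do.

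**What to change.** - **Section 3.7.2:** name one contrast for the 75% interval and MCID reading: the between-group difference in cervicobrachial pain NRS at the initial visit of period 5. This is the outcome section 2 points to, assessed after all four treatment periods. State that this interval favours AMT by chance in 12.5% of null trials. Report all other outcomes and times as descriptive estimates with intervals, not used to claim a trend or pilot success.
- **Abstract:** make the success targets agree with section 4, where better outcomes are a hypothesis, and align the sentence on trends of effectiveness with the named contrast.
- **Section 5:** delete the statement that the 75% level contributes to realistic and unbiased estimates. The level changes interval width and coverage only.

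The cost is wording; the models, data and sample size are unchanged. The downside is that fewer outcomes can be presented as promising.

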**Figure 1 fig1:**
[figure not shown]
pAMTLER study design. CR, cervical radiculopathy; R, randomized allocation; CG, control group; EG, experimental group; V, visit; Peri, period; NRS-CP_p24_, having cervicobrachialgia over the previous 24 h on NRS; +1 d, data premitted to be collected within 1 day after the scheduled time. 

 collecting data on efficacy- and cost-related outcome measures, followed by administering AMT; 

, collecting data on cost-related outcome measures, followed by administering AMT; 

, collecting data on efficacy- and cost-related outcome measures; 

, recording adverse events, adverse reactions and concomitant medication during the trial; 

, receiving usual care for 4 periods. Baseline assessment including socio-demographics (age, sex, education level, employment status, health insurance, etc.), medical history (comorbidities, concomitant medications, details related to the cervicobrachial pain episode, etc.) and physical examination (dominant hand, abnormal deep tendon reflexes, radiculopathy level shown on magnetic resonance imaging, etc.).

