#### AMTs

3.5.2

Participants randomized to the experimental group will receive 14 additional sessions of AMT over the four usual care periods, with one session per day in the first period, three sessions in the second period, and two sessions per period in the remaining two periods. It will be administered by a registered therapist who is blinded to the outcome evaluation. The therapist will be required to complete structured training with a self-developed AMT teaching robot (Patent No. CN202311394450.9, CN202311398626.8) and become familiar with the AMT procedure before participating in the pAMTLER.

AMT methodology

This composite intervention procedure begins with pressing-kneading manipulation, is followed by traction manipulation, and concludes with mechanical traction (Appendix S5).

Pressing-kneading manipulation (Figure 4) refers to pressing and kneading the participant’s nuchal region, which is bounded by the 7th cervical vertebra horizontal level and the bilateral mastoid process vertical lines, with the neck anteriorly flexed. The participants will lie supine on the therapy table, with pillows used to gently elevate their heads and necks until the neck is anteriorly flexed to an angle that relieves pain or numbness in the cervicobrachial region. The therapist will sit on a chair at the cranial end of the therapy table, close to the participant’s head. With the palm of one hand supporting the participant’s occiput, the therapist will sequentially perform pressing-kneading along the transverse, zygapophyseal, and spinous process lines within the defined nuchal region using his other hand. He should use the pulps of the index, middle, and ring fingers to press and knead the nuchal muscles along these three process lines in an upward and inward direction, from lateral to medial. To alleviate any muscle tension around the nuchal region, the knead-pressing should be administered at a rate of 30 times per minute, with 3 repetitions on each side. The pressing-kneading force applied should be within the participants’ tolerance, allowing them to feel comfortable and relaxed. Additionally, any tender points identified during knead-pressing should be massaged at a frequency of 50 times every 30 s.

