#### Primary outcome measurements

3.6.1

Measures that indicate the feasibility of the future full-scale RCT will serve as primary outcomes. They will be:

enrolment rate: the proportion of recruited participants who are randomized.weekly enrolment rate: the number of participants to be randomized per week over the trial recruitment duration.drop-out rates: the proportion of participants who either withdraw or are lost to follow-up at the initial visits of the 2nd, 3rd, 4th, or 5th periods.retention rates: the proportion of non-dropout participants (i.e., those completing all follow-up measurements) at the initial visits of the 2nd, 3rd, 4th, and 5th periods.adherence rates: the proportion of participants completing the planned number of treatment sessions after randomization (the proportion completing 14 sessions of AMT in the experimental group and attending 4 usual care prescriptions in the control group, respectively).completion rates of efficacy-related outcome measures: the proportion of completed efficacy outcome measures relative to those intended for assessment at the initial visit per period.completion rates of cost-related outcome measures: the proportion of completed cost outcome measures relative to those intended for assessment at every visit during the trial.

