The TMG assumes responsibility for day-to-day trial operations. It will consist of a project manager, a registered research physician, a registered therapist, a trial coordinator, two research assistants and a data manager. All members will attend a pre-trial training workshop to familiarize themselves with the trial implementation process, and to ensure adherence to the study protocol and standard operating procedures. The trial coordinator is to formulate follow-up programs based on the study protocol. They will keep in touch with participants to facilitate their attendance at scheduled follow-ups, but also to assist in promptly detecting any AE. The research assistants will collect and record data on paper case report forms (CRF), including participants’ socio-demographics (age, sex, education level, employment status, health insurance, etc.), medical history (comorbidities, concomitant medications, details related to the cervicobrachial pain episode, etc.) and physical examination at baseline (dominant hand, abnormal deep tendon reflexes, radiculopathy level shown on magnetic resonance imaging, etc.) and discharge (abnormal deep tendon reflexes), secondary outcomes, treatment information, and adverse event details. Data may be collected within 1 day after the scheduled time. Unless they explicitly refuse, research assistants will follow up with any withdrawn participants to acquire data until the trial end. Additionally, they will track any AE from reporting until resolution. The data manager will regularly monitor data quality, working with research assistants to recover missing data and clarify ambiguous data to ensure all reported data are accurate, complete, legible and verifiable from source documents. Research assistants will double-enter the data from the paper CRF after monitoring into an Epidata-based electronic data capture system. Any discrepancies from double entry will be verified against the paper CRF. The data manager will lock the electronic data capture after all data have been cleaned; researchers will be unable to modify the data. The TMG will meet weekly to review study progress during the trial. The project manager will meet with the TSC biweekly to align on key decisions.

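### The AMT arm has about 15 scheduled contacts and the control arm about 5, with no common adverse-event enquiry stated, so a difference in adverse event rate may partly reflect ascertainment

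*Protocol article*

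**What the plan says.** **Visits.** Section 3.1 of the protocol article describes the schedule as follows: "In this five-period (7 days per period) trial with a total of 15 visits". It does not say to which arm the total applies. Section 3.5.2 gives the AMT arm 14 sessions, "with one session per day in the first period, three sessions in the second period, and two sessions per period in the remaining two periods". For the control arm, the adherence definition in section 3.6.1 counts "attending 4 usual care prescriptions in the control group". Section 3.5.1 adds a fifth-period visit at which leftover analgesics are handed back. Efficacy outcomes are fixed to the first visit of each period in both arms (sections 3.1 and 3.6.2).

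**Adverse events.** The Figure 1 legend has "recording adverse events, adverse reactions and concomitant medication during the trial". Section 3.6.2 defines an adverse event broadly, as any unwelcome experience after enrolment, and says that all are to be recorded. Section 3.8 says of the trial coordinator: "They will keep in touch with participants to facilitate their attendance at scheduled follow-ups, but also to assist in promptly detecting any AE". None of these provisions separates the arms, and none gives a frequency of contact or a form of enquiry.

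**Analysis.** Section 3.7.2: "The remaining secondary outcome measures involving AER, ARR, and intervention costs, as well as baseline variables, will be presented descriptively by the groups". No test, interval or decision rule is attached to AER or ARR.

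**The concern.** Short-lived or minor events tend to be recorded when someone is present to hear of them. An AMT participant can mention such an event on any of seven days in the first week; a control participant is described as seen once. If true risk were equal, more frequent contact would tend to raise the recorded rate in the AMT arm.

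Efficacy outcomes are protected from this by a visit schedule common to both arms. AER has no such anchor in the text, yet it is shown by group. Section 5 expects the pilot to yield preliminary safety information on AMT, and section 3.8 has the steering committee review safety data with no independent monitoring committee. Both uses would be helped by knowing how much of any difference in AER is detection.

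**Working it through.** **1. Reproduce the plan's visit count.** Inputs: session schedule (section 3.5.2) and the fifth-period visit (section 3.5.1). The first visits of periods 1 to 4 coincide with AMT sessions.

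- AMT arm: 7 + 3 + 2 + 2 = 14 sessions; 14 + 1 = 15 visits. This matches section 3.1.
- Control arm (inferred): 4 usual-care attendances + 1 fifth-period visit = 5.

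| Period | AMT | Control (inferred) |
|---|---|---|
| 1 | 7 | 1 |
| 2 | 3 | 1 |
| 3 | 2 | 1 |
| 4 | 2 | 1 |
| 5 | 1 | 1 |
| Total | 15 | 5 |

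The ratio is 15/5 = 3.0. After the first visit it is 14/4 = 3.5. The Figure 1 legend fits this count: the visit types it lists are outcome and cost data followed by AMT, cost data followed by AMT, and outcome and cost data alone. Every visit beyond the one per period therefore involves AMT.

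**2. Look for a channel that is equal by arm.**

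- The daily diary (section 3.5.1) goes to everyone, but its listed items are analgesics, collar hours and pillow use, not adverse events.
- The research physician sees both arms, but section 5 limits his enquiry to whether pain has improved.
- The coordinator (section 3.8) has adverse-event detection as a purpose in both arms, with no stated frequency. The coordinator also escorts participants to visits (section 5), so that part of the contact rises with the number of visits.

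The coordinator is therefore a possible equaliser of unknown strength.

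**3. Illustrate the possible size.** All inputs here are assumptions; the documents give none. Let the true risk be 30% in both arms, and let visits capture a fraction v of events: 0.95 with frequent contact and 0.60 with weekly contact. Let r be the share of events missed at visits that is recovered equally in both arms by coordinator contact or spontaneous report. Then:

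recorded rate = 0.30 × [1 − (1 − v)(1 − r)]

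| r | AMT | Control | Ratio |
|---|---|---|---|
| 0 | 28.5% | 18.0% | 1.58 |
| 0.5 | 29.2% | 24.0% | 1.22 |
| 0.8 | 29.7% | 27.6% | 1.08 |
| 1 | 30.0% | 30.0% | 1.00 |

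With 24 per arm, r = 0 gives 24 × 0.285 = 6.8 against 24 × 0.180 = 4.3 participants.

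A more extreme model supposes that events surface only at visits, each post-baseline visit having the same independent chance q of yielding one. Then 1 − (1 − q)^k with k = 14 and 4 gives 24.6% v 7.8% at q = 0.02 and 77.1% v 34.4% at q = 0.10, ratios of 3.2 and 2.2. This ignores that a weekly visit can recall a whole week, and it ignores the coordinator, so it is an outer case.

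**The case against.** A reader might infer that events are picked up only at visits, that the AMT arm will therefore show the higher AER, and that the safety comparison is confounded beyond use. The documents do not support that.

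- No section ties event capture to visits. Recording runs through the trial, every event is to be recorded, and the coordinator's role in section 3.8 has detection as a second purpose beside attendance.
- The control count is inferred; no section states it.
- Section 5 promises preliminary safety data, not a between-arm estimate. The presentation is descriptive, and the success criteria in section 4 rest on enrolment, adherence and retention.
- Adverse reactions are by definition linked to the intervention, so part of any ARR difference is exposure to AMT and not detection.
- The SPIRIT schedule (Figure 2), Appendix S3 and the operating procedures are not shown and may fix a common enquiry. Its absence from an article is not in itself a fault.
- With 24 per arm, sampling error is large. For example, 36% v 28% has a 95% half-width of 1.96 × √(0.36×0.64/24 + 0.28×0.72/24) ≈ 26 points.

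All of this stands, and it limits the point to a possible partial bias of unknown size. What it does not remove is the imbalance itself, which follows from the stated schedule. Descriptive presentation does not cure it, since two adjacent rates will be compared. Nor can the detection share be separated afterwards unless the record shows how each event was found.

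**Conclusion.** The point holds in a limited form. Scheduled contacts are about 15 v 5, and AER is shown by group with no stated common enquiry. A difference in AER, mainly for minor or transient events, may partly reflect ascertainment. The likely direction is towards a higher rate in the AMT arm, but the size may be anything from nil to large and cannot be determined from the documents. It depends on how much the coordinator's contact recovers in each arm.

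The conclusion rests on the inferred control count and on no common elicitation schedule existing in the parts not shown. It applies to AER; ARR is not a like-for-like comparison in any case, because only one arm is exposed to AMT. No stated feasibility decision turns on it.

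**What to change.** Unless the operating procedures already do so, ask both arms the same scripted adverse-event question covering the previous 7 days, before treatment, at the initial visits of periods 2 to 5. Four 7-day windows cover the 28 treatment days. For each event, record how it was found and at which contact.

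Report AER from all recorded events as planned. Add a between-arm AER limited to events elicited at the common visits, and list separately the events found only at other AMT sessions, for example per session. Keeping the all-events rate matters, because a rate built on weekly recall alone could lose transient reactions seen during a session. Serious adverse event capture and ARR reporting stay as planned, with a note that ARR does not compare like with like.

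The cost is one question at visits that already take place and one extra line in the safety table. Section 4 reports 33 patients recruited by 31 July 2025. For participants who have already finished, the split is possible only where the case report form shows the visit at which the event was detected.
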